**Assessments**					
Gesture tests	**X**	**X**	**X**	**X**	**X**
Clinical rating scales	**X**	**X**		**X**	**X**
Community functioning		**X**		**X**	**X**
Neuroimaging		**X**		**X**	

Secondary outcomes will include additional nonverbal communication, cognitive, clinical, and functional assessments, as well as self-reports. Nonverbal communication will be tested with the Profile of Nonverbal Sensitivity (PONS) (78) assessing nonverbal social perception, and the modified postural knowledge task (79, 80) measuring gesture perception. Together, TULIA, PKT, and PONS assess nonverbal communication, as they include the *production*, the *recognition*, and the *interpretation* of gestures. History of symptoms and medication in patients will be assessed with The Comprehensive Assessment of Symptoms and History (CASH) (81). Self-reports, clinical scales, motor scales, cognitive tests and functional assessments are listed in Table 4.

**TABLE 4 T4:** Primary and secondary outcomes.

Assessments		References
Self-reports	Brief Assessment of Gestures (BAG)	(95)
	Self-report of negative symptoms (SNS)	(96)
	The satisfaction with therapy and therapist scale-revised (STTS-R) for group psychotherapy	(97)
Psychopathology	Positive and negative syndrome scale (PANSS)	(98)
	Brief negative symptom scale (BNSS)	(99)
	Thought and language disorder (TALD)	(100)
	Frontal assessment battery (FAB)	(101)
	Bern psychopathology scale (BPS)	(102)
Motor scales	Neurological evaluation scale (NES)	(103)
	Bush Francis catatonia rating scale (BFCRS)	(104)
	Salpêtrière retardation rating scale (SRRS)	(105)
	Unified Parkinson’s disease rating scale (UPDRS)	(106)
	Abnormal involuntary movement scale (AIMS)	(107)
Behavioral tests	Postural knowledge test (PKT)	(79)
	Profile of nonverbal sensitivity (PONS)	(78)
	Coin rotation	(108)
	Test of Upper Limb Apraxia (TULIA)	(77)
Neuro- and social cognition	Mayer-Salovey-Caruso Emotional Intelligence Test (MSCEIT)	(109)
	Digit span backward (DSB)	(110)
	Test of nonverbal Intelligence (TONI)	(111)
	EMOREC-B	(56)
	Hinting task (HT)	(112)
	EmBODY tool	(113)
Functional assessments	Global assessment of functioning (GAF)	(88)
	Social and occupational functioning assessment score (SOFAS)	(114)
	Personal and social performance (PSP)	(114)
	University of California, San Diego performance-based skills assessment brief (UPSA-b)	(115)
	Social level of functioning (SLOF)	(116)

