**FIGURE 2 F2:**
[figure not shown]
Three fMRI gesture tasks—experimental setup. **(A) Gesture planning/performance task** with the modified Test of Upper Limb Apraxia (TULIA). Participants will be presented with 20 hand gestures in a random order (e.g., wave good-bye) and 10 control sentences with no gesture performance expected (e.g., “the airline flight is delayed”). Each trial will start with an instruction (3 s), followed by a triangle (planning phase: 3 s), then a 3–10 s interstimulus interval with a fixation cross (3–10 s), a circle (execution phase: 3 s), another 3–6 s interstimulus interval, and then a new gesture of the next trial is presented. **(B) Gesture perception task** with the modified Postural knowledge task (PKT). Each trial will start with a fixation cross (3–10 s) followed by a picture (max. 5 s) where the hand of the presented figure will be removed. Participants’ task is to choose the correct hand gesture provided below using button presses of a hand pad inside the scanner (1, 2, and 3) and respond while the picture is still displayed. In the example provided the correct gesture is number two. **(C) Gesture interpretation task** with point-light displays (PLD). Each trial will start with a fixation cross (3–10 s) followed by a PLD video, after which a question mark will be displayed (3 s). The video will include two PLD figures: one on the right side and the other on the left side of the screen. During the video, one PLD will perform a gesture while the other PLD will either follow or imitate these performed gestures. Participants’ task will be to indicate with the button press of a hand pad which of the two PLD figures (left or right) is imitating or following the gestures of the other when the question mark will be displayed. The gray connecting lines and the two gray circles (i.e., PLDs’ heads) are a visual aid and will not be present in the actual experiment.

Outcomes will be measured during four different time points: baseline, after cTBS (week 2), after SCRT (week 8) and follow-up (week 32) (see Table 3). At baseline, week 8 and week 32, the primary and all secondary outcomes will be tested. At week 2, the primary and a few secondary outcomes (i.e., nonverbal communication and clinical assessments) will be measured. Additionally, at baseline and week 8, neuroimaging data will be acquired to test the neural effects of the treatments.

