### Statistical Considerations and Plan

Assuming a medium effect size (*f* = 0.15) in a repeated measures ANOVA with moderate-high correlation between time points (0.75), a power of 0.95 and an alpha = 0.05, we will need 72 patients (24 per group). In addition, a control group of 24 healthy subjects will be required. All four groups will be compared pre-to-post with an interval of 8 weeks (see Figure 1). The main effects of the combined interventions on the primary and secondary outcomes will be calculated in a repeated measures design including 3 main time points (Baseline, week 2, and week 8) and three patient groups (A, B, and C). With the latest SPSS and R versions, we also will run additional (partial) correlations, linear regressions, MANCOVAS using covariates (e.g., age, education, and medication).

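### The three-visit model stated for the A/B/C effect cannot be fitted to functioning or cognition, which have no week-2 measurement

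*Protocol article*

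**What the plan says.** **Model.** Statistical Considerations and Plan says of the analysis: "main effects of the combined interventions on the primary and secondary outcomes will be calculated in a repeated measures design including 3 main time points". It names these as baseline, week 2 and week 8, and applies them to groups A, B and C. No outcome is excepted. The same section announces a pre-to-post comparison of all four groups over 8 weeks, the fourth being healthy controls, and further correlations, regressions and MANCOVAs with covariates.

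**Visit schedule.** In Behavioral and Clinical Assessments, the paragraph after Figure 2 says: "At week 2, the primary and a few secondary outcomes (i.e., nonverbal communication and clinical assessments) will be measured". It places the primary outcome and the full set of secondary outcomes at baseline, week 8 and week 32. In Table 3, the row "Community functioning" is marked at baseline, week 8 and follow-up, and its week-2 cell is empty.

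**Aims.** Aims and Hypotheses puts gesture performance and social functioning together in the main goal and predicts A > B > C for both. TULIA is the only primary outcome.

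**Sample size.** "Assuming a medium effect size (*f* = 0.15) in a repeated measures ANOVA", with a "moderate-high correlation between time points (0.75") and with "a power of 0.95 and an alpha = 0.05", the article concludes that "we will need 72 patients (24 per group"). The calculation names no outcome.

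**The concern.** The model for the randomised comparison and the visit schedule do not fit together. For functioning, every patient lacks one of the three required visits by design. A repeated measures ANOVA on complete cases would keep nobody, and a mixed model would have no data from which to estimate arm effects at week 2.

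Functioning is one of the two outcomes in the main goal and has its own ordered hypothesis, yet the analysis meant to test that hypothesis has to be replaced by one that the article does not name. Several replacements are open: change to week 8 in three arms, week 8 adjusted for baseline, weeks 8 and 32 together, or the four-group comparison. These are different tests and can give different answers, so the choice should be fixed before the data are seen. A reader may also take the 0.95 to cover all outcomes placed in that model.

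**Working it through.** **1. Which outcomes have the three visits**

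| Outcome | Baseline | Week 2 | Week 8 | Source |
|---|---|---|---|---|
| TULIA | yes | yes | yes | text and Table 3 |
| Functioning | yes | no | yes | text and Table 3 |
| Cognition | yes | no | yes | text only; no row in Table 3 |
| Clinical ratings | yes | text yes, Table 3 blank | yes | the two disagree |
| Self-reports | yes | not stated | yes | text only; no row in Table 3 |

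The model fits TULIA. It does not fit functioning (explicit in both places) or cognition (by the text). For clinical ratings the article contradicts itself. For self-reports nothing firm can be said.

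**2. What the other stated comparison tests**

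The pre-to-post comparison uses baseline and week 8, so functioning data can enter it. Its overall group-by-time test covers A, B, C and healthy controls. It can be significant because patients change differently from untreated healthy people, even if A, B and C do not differ. It is therefore not the randomised test.

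**3. Reproducing the stated figure**

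Inputs from Statistical Considerations and Plan: f = 0.15, correlation ρ = 0.75, alpha = 0.05, N = 72, k = 3 groups, m = 3 visits. For the group-by-time interaction under sphericity:

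- λ = f² × N × m / (1 − ρ), df1 = (k − 1)(m − 1), df2 = (N − k)(m − 1)
- λ = 0.0225 × 72 × 3 / 0.25 = 19.44; df = 4 and 138
- Power = 0.952. The smallest balanced N reaching 0.95 is 72.

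This matches the article, so the 72 is consistent with three arms and three visits.

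**4. The same inputs with two visits** (assumes that f and ρ carry over to functioning)

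- λ = 0.0225 × 72 × 2 / 0.25 = 12.96; df = 2 and 69
- Power = 0.894. Reaching 0.95 would take 90 patients (30 per group).

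Sensitivity to ρ at N = 72: 0.5 gives 0.60, 0.6 gives 0.70, 0.7 gives 0.83, 0.8 gives 0.95.

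**5. Week 8 with baseline as covariate, same inputs**

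A change score has variance 2σ²(1 − ρ). Week 8 adjusted for baseline has residual variance σ²(1 − ρ²). The noncentrality rises by the ratio 2(1 − ρ)/(1 − ρ²) = 2/(1 + ρ) = 2/1.75 = 1.143.

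- λ = 12.96 × 1.143 = 14.81; df = 2 and 68
- Power = about 0.93.

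**6. The four-group pre-to-post comparison**

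With 72 + 24 = 96 participants: λ = 0.0225 × 96 × 2 / 0.25 = 17.28; df = 3 and 92; power = 0.942. This describes a test that includes the healthy controls, not the A/B/C test.

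**The case against.** A reader might infer that functioning has no analysis at all. The article does not support that. Its pre-to-post comparison over 8 weeks contains arms A, B and C, and functioning is measured at both ends; regressions and MANCOVAs are mentioned too. What is missing is a named three-arm test that the schedule allows.

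A reader might also infer that the article claims 0.95 power for functioning or that the trial is too small. It does neither. The calculation names no outcome, and TULIA, the sole primary outcome, has its week-2 value.

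It is equally tempting to add self-reports to the affected outcomes. That would be a guess: a gesture or negative-symptom self-report could count as nonverbal communication or clinical assessment at week 2.

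The best remaining defence is that the two passages can be read together, with the three-visit model for outcomes that have three visits and pre-post for the rest, and that allocating models to outcomes is detail for a full protocol or analysis plan. This carries some weight, since dropping week 2 leads naturally to baseline and week 8. But the article makes no such split: it assigns primary and secondary outcomes alike to the three-visit model. That is a stated rule in conflict with the stated schedule, not an omitted detail. The pre-post comparison it would fall back on is the one that includes healthy controls.

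**Conclusion.** The point holds in limited form. The model stated for the A/B/C effect cannot be fitted to functioning or, by the text, to cognition, and the three-arm week-8 analysis that would take its place is neither named nor powered. This touches an outcome in the main goal but not the primary outcome: the TULIA analysis and the 72 patients stand.

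The 0.95 belongs to three arms and three visits. On the same inputs, the shortfall is about 6 percentage points for a two-visit pre-post test (0.952 − 0.894) and about 2 with baseline as covariate (0.952 − 0.931). These figures assume complete data on 72 patients and that f = 0.15 and ρ = 0.75 hold for functioning. The article does not say so, and the result depends strongly on ρ. They show that the 0.95 does not transfer; they are not power values to be reported for functioning without support for those inputs.

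**What to change.** In Statistical Considerations and Plan:

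1. Limit the baseline, week 2 and week 8 model to outcomes measured at week 2.
2. For functioning and cognition, name a three-arm analysis of the week-8 value with the outcome's own baseline as covariate. Let the week-8 arm contrast decide, and report week 32 for durability.
3. Say that the four-group pre-to-post comparison sets patients against healthy controls and is not the test of treatment effect.
4. State that the 0.95 is a three-visit figure that does not apply to functioning or cognition. If power is given for them, state the assumed effect size and correlation and use the model named in item 2.
5. Reconcile the text after Figure 2 with Table 3 on whether clinical ratings are taken at week 2, so that it is clear which model they fall under.

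The cost is analysis wording. No new data or patients are needed. The price is a less favourable power statement for functioning and cognition.

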### Primary and Secondary Outcomes

#### Behavioral and Clinical Assessments

The primary outcome of this study will be hand gesture performance, which will be assessed with the Test of Upper Limb Apraxia (TULIA) (77). TULIA includes 48 items in two domains: Imitation (following demonstration) and pantomime (after verbal command). The test has three semantic categories of gestures: communicative (intransitive), object-related (transitive), or meaningless. Item ratings range from 0 to 5. If the participants make content errors (e.g., perseverations, substitutions), they will get 0–2 points per item. If the participants make spatial or temporal errors, they will get 3–4 points. Perfect performance equals 5 points, which is the maximum score per item. The highest TULIA total score is 240. A cutoff score will be used to measure gesture deficits in schizophrenia with < 210 TULIA total score (17). Gesture performance will be recorded on video and later evaluated by an independent examiner who is blinded to the groups or timing of the assessment. We will assess gesture performance using TULIA at four different time points (see Table 3).

**TABLE 3 T3:** Time-points of assessments.

	Screening	Baseline	Week 2 tests	Week 8 tests	Follow-up
TIME (week)	–4 to 0	0	2	8	32

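### Baseline TULIA is an outcome level and is not named as a covariate: the test is valid and powered as stated, but at the plan's correlation of 0.75 it loses about 5% to 17% of the information, and the text does not name the effect that gave 72 patients

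*Protocol article*

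**What the plan says.** All of this stands in the protocol article, mostly under Statistical Considerations and Plan.

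- **Sample size.** The calculation starts from "Assuming a medium effect size (*f* = 0.15) in a repeated measures ANOVA". It adds a correlation of 0.75 across visits, 95% power and a 5% significance level, and concludes "we will need 72 patients (24 per group").
- **Main analysis.** The stated target is "The main effects of the combined interventions on the primary and secondary outcomes". For arms A, B and C, the plan is that these are "calculated in a repeated measures design including 3 main time points (Baseline, week 2, and week 8").
- **Covariates.** These appear only among additional analyses, as "MANCOVAS using covariates (e.g., age, education, and medication"). The Advantages section adds gender, and Limitations specifies olanzapine equivalents for antipsychotic medication. Baseline TULIA is named nowhere as a covariate.
- **Primary outcome.** "The primary outcome of this study will be hand gesture performance, which will be assessed with the Test of Upper Limb Apraxia (TULIA"). The hypothesis under Aims and Hypotheses is an ordering of the arms after treatment, A over B over C.

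The arm-by-time interaction is not named anywhere.

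**The concern.** Baseline is measured before treatment, so randomisation makes its expected value equal in all arms. If it is a response level, the arm-by-time test becomes a comparison of raw changes. Subtracting the full baseline value is optimal only when the correlation with follow-up is 1. At 0.75 it subtracts too much and adds noise. A regression on baseline subtracts the right fraction and is never worse in large samples.

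Three things follow:

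- precision is lost from data the trial already collects;
- a chance baseline difference between arms of 24 is over-corrected in the change contrast;
- the effect named in the text is not the one that gives the sample size, so a reader cannot tell which test is primary.

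**Working it through.** **Inputs from the plan:** f = 0.15, correlation ρ = 0.75 between visits, α = 0.05, N = 72 in k = 3 arms of 24, m = 3 visits. Outcomes are in SD units with equal variances and sphericity.

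**1. The plan's own figure.** Arm-by-time interaction:

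- λ = f²·N·m/(1−ρ) = 0.0225 × 72 × 3 / 0.25 = 19.44
- df = (k−1)(m−1) = 4 and (N−k)(m−1) = 138
- power 0.952; the smallest N with three equal arms that reaches 0.95 is 72

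The stated figure is reproduced. With the same inputs, an arm main effect would need 576 patients and a time main effect 60.

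**2. One week-8 contrast.** Per-patient variance:

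- change from baseline: 2(1−ρ) = 0.50
- adjusted for baseline: 1−ρ² = 1−0.5625 = 0.4375
- ratio 0.4375/0.50 = 0.875, so 12.5% lower with adjustment. Equivalently, 72 patients analysed by change carry the information of 72 × 0.875 = 63 analysed with adjustment.

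**3. Joint week-2 and week-8 test.** The covariance of the two changes is [[0.50, 0.25], [0.25, 0.50]]. Adjusted for baseline it is [[0.4375, 0.1875], [0.1875, 0.4375]]. For an effect shape t over the two visits, λ is proportional to t′V⁻¹t. Each shape is scaled so that the interaction has f = 0.15, which gives λ = 19.44 and power 0.952 for the stated analysis.

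| Effect shape (week 2, week 8) | t′V⁻¹t, change | t′V⁻¹t, adjusted | λ adjusted | Information lost by using change | Power adjusted |
|---|---|---|---|---|---|
| Week 8 only (0, 1) | 2.667 | 2.80 | 20.41 | 1−19.44/20.41 = 4.8% | 0.962 |
| Linear by visit (0.5, 1) | 2.00 | 2.30 | 22.36 | 1−19.44/22.36 = 13% | 0.975 |
| Sustained from week 2 (1, 1) | 2.667 | 3.20 | 23.33 | 1−19.44/23.33 = 16.7% | 0.980 |

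With adjustment, power 0.95 is reached with 69, 63 or 60 complete patients respectively.

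**4. Chance imbalance.** The baseline difference between two arms of 24 has SD √(2/24) = 0.29. Given a difference d, the change contrast is shifted by −(1−ρ)d = −0.25d. For a 1-SE imbalance that is 0.25 × 0.29 = 0.07 SD, against the arm that started higher.

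**5. Main effects read literally.** For the arm main effect, λ = f²·N·m/(1+(m−1)ρ) = 0.0225 × 216 / 2.5 = 1.94, with df 2 and 69, and power is 0.21. This reuses the interaction's f for a different effect. If the true effect is instead fixed so that the interaction has f = 0.15 and the arms are equal at baseline, the arm main effect has power:

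- 0.39, sustained from week 2
- 0.30, linear by visit
- 0.21, linear by week
- 0.13, week 8 only

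Dropping the baseline visit and keeping f = 0.15 gives 0.0225 × 72 × 2 / 1.75 = 1.85 and power 0.20.

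**The case against.** The strongest reply is that the stated analysis does what it claims: the interaction test is valid, is unbiased under randomisation and reaches 0.95 under the plan's assumptions. That stands. Adjustment moves power only from 0.952 to between 0.962 and 0.980.

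A second reply is that a repeated measures design with three visits does not exclude a model with baseline means constrained equal, that the covariate list is only illustrative, and that a fuller plan may settle this. In part that also stands. But the article does choose baseline as a response level, and a plain repeated measures ANOVA, the method used for the sample size, has no such constraint. The point concerns a stated choice with a better alternative, not a missing detail.

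Four stronger readings are tempting, and the document does not support them.

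- **The trial has power of only 0.21.** This takes main effects in the ANOVA sense. The sample size fits the interaction exactly, and the same sentence uses main for the principal time points, so the wording may simply be loose. Nor is the low figure caused by including baseline, since without it the power is 0.20.
- **Up to 20% of the information is discarded.** The values 5%, 15% and 20% are gains in noncentrality from adjusting. The matching losses are 4.8%, 13% and 16.7%.
- **Baseline imbalance goes uncorrected.** The change contrast over-corrects by a quarter of the difference. This is a conditional shift, not a bias over repeated randomisations.
- **Adjustment would absorb the expected dropout.** Limitations says only that dropout may be high and gives no rate. The saving is 3 to 12 of 72 complete patients, and nothing in the document allows it to be set against losses.

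**Conclusion.** The point holds as a loss of precision plus an ambiguity about the primary test. It does not show an invalid or underpowered analysis. At ρ = 0.75, adjustment lowers the variance of each week-8 contrast by 12.5%. The stated joint test discards about 5% to 17% of the information, depending on the effect shape. A 1-SE baseline imbalance shifts a change contrast by about 0.07 SD.

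These figures assume equal variances, the same correlation between all pairs of visits and complete data. The loss for a single contrast is (1−ρ)/2, so it would be larger if the true correlation is below 0.75 and smaller if it is above.

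The wording needs correcting in any case. A literal arm main effect mixes the untreated visit with the treated ones and has power of about 0.13 to 0.39 for an effect consistent with the powered interaction. The time main effect is not a comparison of arms.

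**What to change.** State the primary model as follows:

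- TULIA at weeks 2 and 8 as outcomes;
- baseline TULIA as a covariate, or baseline kept in the response with its mean constrained equal across arms;
- arm, visit and arm-by-visit as fixed effects, with an unstructured covariance within patient;
- treatment effects reported as adjusted arm differences at each visit, in place of main effects.

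Use the same form for secondary outcomes, each with its own baseline value where one is measured. Where an outcome is not assessed at week 2, week 8 alone is the response. If the sponsor prefers to keep the repeated measures ANOVA, the text should at least name the arm-by-time interaction as the test behind the 72 patients.

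The cost is a change of analysis wording, best made before any comparison by arm. It needs no new data, visits or patients.

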### Trial Status

Study recruitment started on the 17th December 2019. The first group started with both interventions on the 24th February 2020. The study was impacted by the federal measures against the COVID-19 pandemic. As of June 2022, we recruited 65 patients and 36 healthy controls. We completed baseline assessments with 62 patients and 33 healthy controls. We finished week-8 assessments with 36 patients and 32 controls.

## Discussion

### Relevance of the Current Study

With this study, we will run one of the few prospective, sham-controlled RCTs addressing both gesture deficits and poor functioning in schizophrenia. Ameliorating functional outcome as a means of reintegrating patients into society has become one of the most central goals of psychiatric rehabilitation (87–89). Despite advances in antipsychotic medications and psychotherapies, functional recovery rates of schizophrenia patients have not increased substantially over the last 30 years (90, 91). Schizophrenia is not only a major burden for patients, but also a great economic strain for society, as patients with schizophrenia make heavy use of inpatient services and require financial support. It is urgent to develop psychiatric treatments that help patients to maintain interpersonal relationships and facilitate independent living. As gesture deficits in schizophrenia are highly correlated to overall functioning in daily life (20) and effective therapies reducing nonverbal communication deficits are lacking, it is clear that we need to establish interventions that tackle both (46, 92).

